### Randomisation

The population was randomized according to the alternate month design method in two arms: experimental and active comparative arm. Weingarten, highlight that’s it’s possible to avoid contamination between the 2 groups with a therapeutic window between the intervention period and control period [29]. This methodology was previously used with good level of evidence in a self-management education program and low back pain treatment in a spa therapy resort [30]. Individual randomization suggests recruitment difficulties (incomplete intervention group risk) and feasibility, as well as an increase in the number of patients lost to follow-up in the control group.

The randomisation list will be established by the methodologist in charge of the project before starting the trial. Population groups will be assigned to arms by stratified randomization by center: this randomization allows for controlling eligibility and for communicating some information relative to randomisation from the investigator and eventually other actors. A document detailing the procedures for randomisation is kept confidential. Participants will be allocated to one of two arms (Figs. 1 and 2).

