### Statistical considerations

#### Sample size estimation

According to previous works presented in literature [11], we have estimated that a sample size of *n* = 65 patients per randomized group, for a two-sided type I error at 5%, would provide 80% statistical power of detecting an absolute difference of 20% (25% vs 5.) in the primary outcome: proportion of participants varying to one IPAQ class at least (low-moderate or high or moderate-high). Finally, a total of *n* = 142 patients (71 by group) will be considered to take into account lost to follow-up (10%).

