According to clinical relevance, sub-group analyses depending gender will be proposed after the study of sub-group x randomization group interaction in regression models (for repeated data or not). Secondarily, a per-protocol analysis will be considered. Finally, a sensitivity analysis will be performed and the nature of missing data will be studied (missing at random or not). According to this, the most appropriate approach to the imputation of missing data will be proposed (maximum bias (e.g. last observation carried forward vs. baseline observation carried forward) or estimation proposed by Verbeke and Molenberghs for repeated data). More precisely, concerning the IPAQ score, when participant will mention a number of days, hours or minutes for an activity without checking « yes » or « no » to intense, moderate or walking categories practice, a « yes » response will be imputed to this question. If participant no mentions to the practice of an activity or the number of days, hours or minutes, a « no » response will be imputed to this question.

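### LOCF versus BOCF is given as the example of a maximum-bias analysis, but for the binary primary endpoint the pair does not bound the bias from missing data (minor)

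*Protocol article*

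**What the plan says.** The Statistical analysis section of the protocol article plans a sensitivity analysis and a study of whether data are missing at random. In the light of that study an imputation approach will be proposed. Two routes are named. One is "maximum bias (e.g. last observation carried forward vs. baseline observation carried forward"; the other is a published estimation method for repeated data. The text that follows on the IPAQ concerns yes/no answers to single items. It does not deal with patients who return no 3-month questionnaire.

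The Primary outcomes section defines the endpoint as the proportion moving up at least one IPAQ class at 3 months. The Statistical analysis section tests it by chi-squared or Fisher's exact test, with intention to treat. Sample size estimation assumes an "absolute difference of 20% (25% vs 5.) in the primary outcome", with "65 patients per randomized group" raised to "142 patients (71 by group") to allow for a stated 10% loss. Time-point outcomes places data collection at baseline, after treatment (18 days) and 3 months.

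**The concern.** A maximum-bias analysis should show how far missing data could move the result. For a binary endpoint that limit is known exactly: score all missing patients in one arm as successes and all in the other as failures, then reverse the two. LOCF and BOCF do something else. BOCF returns each missing patient to the baseline class, so each one is a failure whatever the arm. LOCF takes the last class seen, which is day 18 at the latest. Neither rule assigns success to lost controls and failure to lost experimental patients, which is the configuration that most weakens a positive result.

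The reading of the sensitivity analysis is at stake; the primary test is not affected. A reader who sees maximum bias attached to these two methods may take the span between them as the full range that missing data allow, when it can be much narrower.

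**Working it through.** **Inputs** (Sample size estimation, except where noted)
- Design rates: 25% experimental, 5% control; two-sided 5% level.
- 71 enrolled and 65 evaluable per arm, so 71 − 65 = 6 lost per arm (6/71 = 8.5%). The stated 10% of 71 is 7.1, so 7 lost is checked too.
- Tests: chi-squared (uncorrected here) or Fisher (Statistical analysis).
- Assumptions: the observed rates equal the design rates, and loss is equal in the two arms.

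**The plan's own figure.** The usual pooled formula for 25% vs 5% at two-sided 5% gives 49 per arm at 80% power (59 with continuity correction). It gives 65 at 90% power, so 65 is not reproduced at the stated power. That is a separate matter: the check below uses only the rates, the 71 per arm and the loss.

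**Step 1, expected observed counts.** 0.25 × 65 = 16.25, taken as 16; 0.05 × 65 = 3.25, taken as 3. Complete cases are 16/65 vs 3/65: 24.6% − 4.6% = 20.0 points.

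**Step 2, formula.** With a and b responders out of 71, the difference is (a − b)/71, and z = difference / √[p(1 − p) × 2/71] with p = (a + b)/142. Example for 16 vs 9: difference = 7/71 = 0.0986; p = 25/142 = 0.176; standard error = √(0.176 × 0.824 × 0.02817) = 0.0639; z = 1.54; p-value 0.123.

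**Step 3, scenarios with 6 lost per arm**

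| Rule for missing patients | Experimental | Control | Difference (points) | Chi-squared p | Fisher p |
|---|---|---|---|---|---|
| Complete cases | 16/65 | 3/65 | 20.0 | 0.0012 | 0.0022 |
| BOCF | 16/71 | 3/71 | 18.3 | 0.0014 | 0.0023 |
| LOCF, day-18 moves 25% vs 5% (assumed) | 18/71 | 3/71 | 21.1 | 0.0004 | 0.0006 |
| LOCF, day-18 moves 50% vs 5% (assumed) | 19/71 | 3/71 | 22.5 | 0.0002 | 0.0003 |
| Lower bound: experimental fail, control succeed | 16/71 | 9/71 | 9.9 | 0.123 | 0.186 |
| Upper bound: experimental succeed, control fail | 22/71 | 3/71 | 26.8 | <0.001 | <0.001 |

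The 95% interval at the lower bound is −2.6 to 22.3 points. In these scenarios BOCF and LOCF span about 18 to 23 points; the logical range is 9.9 to 26.8.

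**Step 4, where significance goes.** All 6 lost experimental patients fail and k of the 6 lost controls improve, giving 16/71 vs (3 + k)/71:

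| k | Difference (points) | Chi-squared p | Fisher p |
|---|---|---|---|
| 0 | 18.3 | 0.0014 | 0.0023 |
| 3 | 14.1 | 0.020 | 0.035 |
| 4 | 12.7 | 0.040 | 0.067 |
| 5 | 11.3 | 0.073 | 0.116 |
| 6 | 9.9 | 0.123 | 0.186 |

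**Step 5, sensitivity to rounding and loss.** Rounding the experimental count up gives a lower bound of 17/71 vs 9/71: 11.3 points, chi-squared p = 0.083, Fisher 0.128. With 7 lost per arm the lower bound is 16/71 vs 10/71: 8.5 points, chi-squared p = 0.193, Fisher 0.278.

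**The case against.** The strongest reply is that the plan does not commit to this analysis. LOCF and BOCF stand in brackets as an example, an alternative is offered, and the choice is deferred until the missing data have been studied. The sentence covers missing data in general and does not say that the pair is meant for the primary endpoint. A condensed article may also leave the exact scenarios to a fuller document. All of this stands and keeps the point small. It does not rescue the label: the article attaches a specific property to a named pair, and for the primary endpoint the pair lacks it.

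A second reply is that the pair could mean LOCF in one arm and BOCF in the other. With LOCF for controls and BOCF for the experimental arm, the analysis comes nearer the lower bound. It reaches it only if every lost control had already moved up a class by day 18. If patients leave before day 18, or the IPAQ is not collected then, LOCF and BOCF coincide for this endpoint.

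A third reply is that the lower bound is remote. This is fair. Losing significance needs all lost experimental patients to fail and 67% (4 of 6) to 83% (5 of 6) of lost controls to improve, against a planned control rate of 5%. If lost controls improved independently at 5%, the chance of 4 or more out of 6 would be about 0.00009; at the experimental rate of 25% it would be about 0.04.

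A reader might also infer that the protocol expects heavier loss among controls, because the Randomisation section mentions "an increase in the number of patients lost to follow-up in the control group". The subject of that sentence is individual randomisation, the design the authors rejected. It is no evidence about loss in this trial and is not used here.

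**Conclusion.** The point holds as a minor one about a label and its example. For the binary 3-month IPAQ endpoint, LOCF versus BOCF does not bound the bias from missing data. At the design rates with 6 lost per arm, BOCF leaves a difference of 18.3 points (p = 0.001), while the true bounds are 9.9 points (chi-squared p = 0.12, Fisher 0.19) and 26.8 points.

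Two stronger readings are tempting and not supported. One is that the planned result is fragile: it stays significant by both tests even if half the lost controls improved and every lost experimental patient failed. The other is that a positive result would be declared robust on this pair alone; no part of the article says so.

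The figures rest on observed rates equal to the design rates, equal loss of 6 or 7 per arm, and, for the LOCF rows only, assumed day-18 rates.

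**What to change.** In the Statistical analysis section, for the primary endpoint, remove the maximum-bias label from LOCF/BOCF. Define maximum bias instead as missing experimental patients scored as failures with missing controls scored as successes, and give the reverse as the other bound. Present both as the corner cells of a two-way tipping-point table: number of responders among the missing in one arm against the number in the other, with the risk difference and p-value in each cell. With 6 lost per arm that is 7 × 7 = 49 cells. The table lets the reader judge how plausible the cells that lose significance are, so the extreme corner need not be over-read.

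The cost is one extra table and a sentence of wording, with no change to sample size, data collection or the primary test. The statement on robustness may come out somewhat less favourable.

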## Discussion

In the context of an aging population, OA is a high-prevalence disease, whose prevalence will increase in the future [41]. In addition, OA is not limited to joint pain and stiffness, and the health care strategy needs to be standardized and personalized with optimized adherence to treatment [42]. This research question is important because OA lacks a cure, and few solutions to the management of knee OA are offered to patients. Treatments will be based on modifiable risk factors, such as pain, function, obesity, comorbidities, intrinsic barriers to PA practice, and sedentary time [43, 44]. The knee OA population appears to be more affected by these risk factors [45, 46], and the most severely affected patients are the less active ones [12]. The key challenge for OA treatment consists in increasing PA level to decrease the risk factors [47].

This quasi-randomized trial will be the first study to compare the effect of a self-management exercise program associated with spa therapy versus spa therapy alone. The non-invasive, adapted, tailored and original character of the intervention is a novel approach for knee OA management.

STT can improve pain and functional capacity of people with knee OA [14]. PA practice must be the key element in managing knee OA symptoms, according to recommendations [8]. However, many obstacles to exercise have been described [48], such as fears and beliefs about pain, treatment and PA [49]. Hence, changing the PA behaviour of people with knee OA is difficult [50]. Education and self-management are based on the bio-psycho-social model, effective strategies for modifying fears and beliefs and increasing adherence to treatment [51].

This protocol has some limitations. The quasi-randomized method could be a limitation, but this method is the most appropriate to avoid contamination biases between groups [29]. When assessing the effectiveness of non-pharmacological treatments such as behavioral therapy the blinding of participants and care providers is frequently impossible [52–54]. Moreover, the success of the treatment often depends on the skill and experience of care providers [26, 55, 56].

The study could demonstrate that self-management exercise programs offer a complementary therapy to the spa therapy effect could reinforce in the medium term increasing PA level and could ameliorate fears and beliefs, self-efficacy and anxiety/depression.

The findings of this trial could offer new perspectives in establishing best clinical practice guidelines for this patient population.

### Ethics and dissemination

The study protocol was approved by the medical ethics committee of South-East France (Sud-Est 6), no. 2015/CE38, and was registered at ClinicalTrials.gov (NCT 02598804 on November 5, 2015. The trial will be conducted in compliance with both Good Clinical Practices and the Declaration of Helsinki. In accordance with French law, the ethics committee of South-East France (Sud-Est 6) and the study protocol, all patients will provide written consent to participate in the study after being informed in detail about the study procedures. The written consent will be reported in the medical file. The design and conduct of this trial will adhere to the requirements of the Standard Protocol Items: Recommendations for Interventional Trials (SPIRIT). The results will be reported in accordance with the CONSORT Statement for nonpharmacological trials. The results from this study will be disseminated through peer-reviewed publications and presentations at international scientific meetings.

## Abbreviations

ACR: American College of Rheumatology
ASES: arthritis self-efficacy
BMI: Body Mass Index
D: Days
HAD: Hospital Anxiety and Depression Scale
IPAQ: International Physical Activity Questionnaire short form score
ITT: Intention to treat
KOFBeQ: Knee OA Fears and Beliefs Questionnaire
M: month
OA: Osteoarthritis
OARSI: Osteoarthritis Research Society International
PA: Physical Activity
SPIRIT: Standard Protocol Items: Recommendations for Interventional Trials
STT: spa therapy treatment
WHO: World Health Organisation
WOMAC: Western Ontario and McMaster Universities Osteoarthritis Index
